#### 2.6.2. Baseline Visit (Week 0)

After providing written informed consent, participants will undergo a baseline assessment. During this visit, researchers confirm eligibility, assign a unique identification code to ensure confidentiality, and collect baseline data via the eCRF.

The collected data include demographic characteristics (sex, date of birth, and age), anthropometric measurements (height, weight, and body mass index [BMI]), and medical history, including relevant comorbidities and concomitant medications (drug name, dosage, route of administration, indication, and duration of use).

For FD-related history, information regarding symptom onset, prior diagnostic evaluations (including upper gastrointestinal endoscopy findings), previous treatments and responses, and baseline disease characteristics will be documented in detail. Baseline outcome measures include the NRS for dyspepsia severity and the NDI-K.

#### 2.6.3. Treatment and Follow-Up Visits

Participants will return for follow-up evaluations at weeks 2 and 4. These visits involve updating the NDI-K and NRS scores, reviewing changes in herbal prescriptions, and documenting concomitant therapies or adverse events to track the longitudinal impact of treatment. Patient adherence to HDs will be systematically assessed at each follow-up visit based on patient-reported counts of remaining pouches. Unscheduled visits, defined as visits occurring when participants present to the clinic outside of scheduled visit time points, will also be documented to capture all relevant clinical data.

### 2.7. Safety Assessment

Adverse events (AEs) will be monitored at each visit. All AEs will be recorded in detail, including the onset, duration, severity, outcome, and management. AEs will be categorized using version 5.0 of the Common Terminology Criteria for Adverse Events (CTCAE). The causal relationship between AEs and HDs will be assessed independently by the investigators based on their clinical judgment. If necessary, external expert consultation may be sought to confirm the causality assessment. All AEs will be managed with appropriate clinical care until resolution. Any serious adverse event (SAE) must be reported to the Principal Investigator and IRB within 24 h of awareness. As this study reflects routine primary care practice, protocol-mandated laboratory safety tests will not be routinely collected.

### 2.8. Data Collection and Management

Data will be collected using designated research worksheets and patient-reported outcome questionnaires. All clinical information and patient responses recorded on paper worksheets will be entered into a centralized and secure eCRF system by the investigators at each site. The eCRF platform features automated validation rules to prevent data entry errors.

A Data Management Officer at the coordinating center conducts periodic audits. If discrepancies arise, the site Principal Investigator (Clinic Director) at the respective site will be notified to verify the source documents and rectify the electronic records.

All physical worksheets and source documents containing personal information will be pseudonymized using a unique participant identification code and will be transferred to the coordinating center in sealed, secure envelopes. Access to these materials will be restricted to authorized research personnel. Upon receipt, all documents will be stored in locked cabinets in restricted-access rooms to ensure confidentiality. The eCRF data will be stored on a password-protected, encrypted server with restricted access rights. All study materials will be archived for at least five years in accordance with national bioethics and data retention requirements.

### 2.9. Sample Size

This exploratory multicenter observational cohort study will be conducted under routine clinical conditions. Because of the lack of prior data on NDI-K changes in this specific clinical context, a formal power calculation was not performed. Instead, the target sample size was determined based on the design of previous clinical trials for HMs in FD [16] and recruitment feasibility across 23 participating KM clinics.

The dropout rate was conservatively set at 25%. Although previous multicenter clinical trials on FD in KM typically assumed a 20% attrition rate [17], a higher threshold is adopted to reflect the pragmatic nature of this study. Assuming a 25% dropout rate, recruiting 150 participants will yield approximately 112 evaluable participants, ensuring our goal of securing at least 100 fully evaluable cases for the final analysis. Furthermore, based on prior literature in which the standard deviation (SD) of NDI-K score changes was approximately 10–12 points [16], a sample of 112 evaluable participants provides high statistical precision. The expected margin of error for the mean primary outcome change is approximately 1.85–2.22 points at the 95% confidence level, providing reliable parameter estimates for this exploratory study.

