### 2.2. Study Design

This is a multicenter, prospective observational cohort study designed to collect real-world data from routine clinical practice without randomization or blinding. To better reflect routine clinical practice, participants will receive assessments and treatments as part of routine clinical care based on the physician’s judgment. The study will be conducted at 23 KM clinics in different regions of South Korea (Table S1), with Kyung Hee University Korean Medicine Hospital serving as the coordinating center. Participants will undergo individualized KM treatments as determined by their physician, followed by clinical assessments and patient-reported outcome surveys at baseline (week 0), visit 2 (week 2), and visit 3 (week 4). This protocol was developed and reported in accordance with the Standard Protocol Items: Recommendations for Interventional Trials (SPIRIT) guidelines (Table S2).

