### 2.3. Study Participants

#### 2.3.1. Recruitment

Participants will be recruited voluntarily from 23 KM clinics during routine clinical practice. No predefined recruitment quotas will be assigned to the participating centers. Physicians will provide patients who meet the eligibility criteria (Table 1) with a comprehensive information document detailing the scope of the study. Written informed consent will be obtained before any research-related activities commence.

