To account for clinic-level clustering and intra-center correlations across the 23 participating clinics, participating sites will be included as a random effect in the mixed models. Furthermore, to accommodate potential confounding factors and treatment heterogeneity in routine clinical practice—such as baseline clinical characteristics, symptom severity, and concomitant KM interventions—multivariable regression models incorporating these key variables as covariates will be performed. Additionally, exploratory subgroup analyses based on these clinical factors may be conducted to evaluate their potential modifying effects. This approach effectively addresses within-subject correlations and handles missing data under the missing-at-random (MAR) assumption; consequently, no explicit data imputation is performed in the primary model. To test the robustness of the primary outcomes against potential departures from the MAR assumption (e.g., missing not at random), sensitivity analyses will be conducted using multiple imputation (MI) under MAR and pattern mixture models (PMMs) with delta-adjustment. Sensitivity analyses will also be conducted using the per-protocol set (PPS) to verify that the missing data pattern does not substantially alter the main findings. Additionally, paired *t*-tests will be performed as a supplementary analysis to evaluate overall within-subject pre- and post-treatment changes. Furthermore, potential assessment mode differences (in-person vs. telephone follow-up) will be evaluated by including assessment mode as a covariate or subgroup factor in secondary analytic models.

Safety monitoring data will be descriptively summarized, focusing on the frequency, intensity, and causal relationships of any recorded AEs. Exploratory subgroup analyses will also be performed based on whether participants received concomitant KM interventions. Where applicable, differences in the AE incidence rates between these subgroups will be evaluated using the chi-square test or Fisher’s exact test.

The full analysis set (FAS) will serve as the primary population for effectiveness outcomes, whereas the PPS and safety analysis set (SAS) will be used for per-protocol and safety evaluations, respectively. The specific criteria for these sets of analyses are outlined below.

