## 3. Discussion

Although FD is prevalent in KM clinics, prospective, real-world evidence remains limited. Although several multicenter studies have investigated FD, most have been explanatory RCTs focusing on standardized herbal formulas in controlled hospital settings [16,18]. To the best of our knowledge, this prospective observational cohort study is designed to provide valuable real-world evidence on the clinical outcomes and safety of individualized HDs administered in routine primary care.

Unlike traditional RCTs, this study adopts a pragmatic observational design that reflects routine clinical practice, in which treatment strategies are tailored to individual patients and often combined with other KM modalities. By prospectively collecting data from 23 primary KM clinics, this study is expected to provide clinically meaningful insights into current prescription patterns, treatment responses, and safety outcomes in routine clinical settings.

This study has several important policy implications. In South Korea, the national pilot program for health insurance coverage of HDs was recently expanded to include FD as a target condition [11]. Despite the widespread clinical use of HDs in the treatment of gastrointestinal disorders, prospective real-world evidence remains insufficient. Therefore, this study will generate valuable, hypothesis-generating data to support the ongoing national pilot program and inform future healthcare policies and clinical decision-making.

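### The stated 95% margin of error (1.85–2.22 points) assumes 112 independent patients, whereas the planned analysis expects correlation within 23 clinics; it holds only at zero intraclass correlation

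*Protocol article*

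**What the plan says.** Section 2.9 reports no formal power calculation. It bases the target of 150 on the design of earlier trials and on recruitment feasibility. It then gives the expected yield: "Assuming a 25% dropout rate, recruiting 150 participants will yield approximately 112 evaluable participants". Citing earlier literature, it says that "the standard deviation (SD) of NDI-K score changes was approximately 10–12 points", and from these inputs it derives the precision statement: "The expected margin of error for the mean primary outcome change is approximately 1.85–2.22 points at the 95% confidence level". It describes this precision as high and the resulting estimates as reliable for an exploratory study. Section 2.9 mentions no ICC, design effect or clustering.

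Three other places bear on this figure:

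- Section 2.2 (Study Design): "The study will be conducted at 23 KM clinics in different regions of South Korea".
- Section 2.10 (Statistical Analysis) includes site as a random effect in the mixed models, for this reason: "To account for clinic-level clustering and intra-center correlations across the 23 participating clinics".
- Section 2.3.1 (Recruitment): "No predefined recruitment quotas will be assigned to the participating centers".

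**The concern.** The precision statement and the analysis rest on different assumptions. If patients of one clinic resemble each other in their response, 112 patients carry less information about the overall mean change than 112 unrelated patients would. The confidence interval from a model with a random site effect reflects this; the interval forecast in section 2.9 does not. Open recruitment makes unequal clinic sizes likely, and unequal sizes enlarge the effect.

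At stake is how the sample size is described. With no power calculation, the margin is the only quantitative statement of what the sample will deliver, and the description of the precision as high rests on it. A reader who later compares the reported interval with the forecast may find it wider for a reason that could be foreseen from the protocol.

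**Working it through.** **Inputs from the protocol.** Evaluable patients: 150 × 0.75 = 112.5, taken as 112 (section 2.9). SD of change: 10–12 points (section 2.9). Clinics: 23 (section 2.2). Confidence level: 95%, two-sided (section 2.9).

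**Inputs the protocol does not give.** The ICC for clinic and the coefficient of variation (CV) of clinic size. The values below are assumptions, shown as a range.

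**Step 1: reproduce the stated figure.** Margin = 1.96 × SD / √n.

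- SD 10: 1.96 × 10 / √112 = 1.852
- SD 12: 1.96 × 12 / √112 = 2.222

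This matches 1.85–2.22 exactly. A t quantile on 111 degrees of freedom would give 1.87–2.25, so the normal quantile was used, with no design effect.

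**Step 2: allow for clustering, equal clinic sizes.** Mean clinic size m = 112/23 = 4.87. Design effect DE = 1 + (m − 1) × ICC. The margin is multiplied by √DE, and the effective sample size is 112/DE.

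**Step 3: allow for unequal clinic sizes.** DE = 1 + ((1 + CV²) × m − 1) × ICC. For CV 0.8 and ICC 0.10: (1 + 0.64) × 4.87 = 7.99, so DE = 1 + 6.99 × 0.10 = 1.699.

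| Assumed ICC | Assumed CV | DE | Effective n | Margin, SD 10–12 | Wider than stated |
|---|---|---|---|---|---|
| 0 | any | 1.00 | 112 | 1.85–2.22 | – |
| 0.01 | 0 | 1.04 | 108 | 1.89–2.26 | 2% |
| 0.05 | 0 | 1.19 | 94 | 2.02–2.43 | 9% |
| 0.10 | 0 | 1.39 | 81 | 2.18–2.62 | 18% |
| 0.05 | 0.8 | 1.35 | 83 | 2.15–2.58 | 16% |
| 0.10 | 0.8 | 1.70 | 66 | 2.41–2.90 | 30% |

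The last column is √DE − 1; for example, √1.387 = 1.18 and √1.699 = 1.30.

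In these calculations the SD of 10–12 is the total SD, so any between-clinic variance is already inside it. What the stated margin omits is the covariance between patients of the same clinic. Within the range shown, the stated figure is recovered only at ICC = 0.

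**The case against.** The case for leaving the text alone has real substance.

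- **The arithmetic is right on its own inputs.** This stands. The fault is an unstated independence assumption, not a miscalculation.
- **The margin did not set the sample size.** This stands. Section 2.9 takes the target from earlier trials and feasibility and adds the margin afterwards. It names no margin that a wider value would breach. A reader might infer that 150 is too few; the documents do not support that.
- **The analysis already handles clustering.** This stands. The random site effect lets the reported interval reflect clustering whatever section 2.9 forecast. A reader might infer that the final interval will be too narrow; nothing in the plan implies this.
- **Clinics are small, so the effect may be small.** This stands in part. With equal clinics the margin is only 2–9% wider at ICC 0.01–0.05. But the protocol states neither a low ICC nor equal sizes.
- **The model recovers some precision.** This stands in part. Section 2.10 adjusts for baseline and uses week 2 data. The full analysis set needs only one post-baseline measurement, so more than 112 patients may contribute. A mixed model also weights clinics, whereas the unequal-size formula is for a plain patient mean. The uneven-clinic figures are therefore approximate upper figures. Section 2.9, however, uses the raw SD of change and credits none of these gains.

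Two stronger readings are tempting. One is that the stated margin is 37% too small. That needs ICC 0.10 together with CV 1.0, for which the documents give no basis. Even then DE = 1.874 and √DE = 1.37, so the adjusted margin is 37% wider and the stated one is 27% too small (1/1.37 = 0.73).

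The other is that the SD itself is too low, because individualized prescribing in 23 clinics must be more variable than the source, so that a value such as 15 should be used. Section 3 says of several multicenter studies that "most have been explanatory RCTs focusing on standardized herbal formulas in controlled hospital settings" and cites the SD source there. The word most does not fix the setting of any one study, and no comparative SD is given. Section 2.9 admits that prior data for this context are lacking. That is a reason for caution about the SD, but it supplies no larger value.

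**Conclusion.** The point holds as a mismatch between the precision statement in section 2.9 and the model in section 2.10. The margin of 1.85–2.22 points is correct for 112 independent patients and is delivered by this design only if there is no correlation within clinics.

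Under assumed ICCs of 0.01–0.10 and equal clinics, the margin is about 2–18% wider. With CV 0.8 and ICC 0.10 it is about 30% wider, subject to the offsets noted above. The direction follows from any positive ICC; the size rests wholly on ICC and CV values that the protocol does not give. Severity is minor to moderate: one planning figure and the wording built on it are too favourable, while the sample size, the conduct and the analysis are unaffected.

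**What to change.** Keep 150 participants and amend the second paragraph of section 2.9 in one of two ways:

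1. Restate the 95% margin as about 1.9–2.9 points for SD 10–12 and 112 evaluable patients in 23 clinics. State the assumed ICC range (0.01–0.10) and the assumed variation in clinic size (equal sizes up to CV 0.8), and mark both as assumptions.
2. Keep 1.85–2.22 but say that it assumes independent patients and that the interval from the planned model will be wider if outcomes correlate within clinics.

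In either case, soften the description of the precision as high so that it matches the figure given.

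The cost is one reworded paragraph and a slightly less favourable stated margin. No extra patients are needed, and nothing changes in recruitment, data collection or the analysis model.

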### 2.10. Statistical Analysis

Statistical significance will be set at *p* < 0.05. Baseline characteristics will be reported using mean ± SD for continuous data, while categorical data will be summarized as frequencies and percentages.

To assess clinical effectiveness, longitudinal changes in NDI-K and NRS scores across time points will be modeled using MMRM. Specifically, for the primary outcome (change in NDI-K score at week 4), the MMRM will fit categorical visit (weeks 2 and 4), baseline NDI-K score as a continuous covariate, and a visit-by-baseline interaction as fixed effects. The inclusion of week 2 data allows utilization of all longitudinal observations to stabilize covariance estimation and provide unbiased estimates of week 4 changes. An unstructured variance-covariance matrix (or a heterogeneous first-order autoregressive structure [ARH(1)] if the model does not converge) will be applied.

To account for clinic-level clustering and intra-center correlations across the 23 participating clinics, participating sites will be included as a random effect in the mixed models. Furthermore, to accommodate potential confounding factors and treatment heterogeneity in routine clinical practice—such as baseline clinical characteristics, symptom severity, and concomitant KM interventions—multivariable regression models incorporating these key variables as covariates will be performed. Additionally, exploratory subgroup analyses based on these clinical factors may be conducted to evaluate their potential modifying effects. This approach effectively addresses within-subject correlations and handles missing data under the missing-at-random (MAR) assumption; consequently, no explicit data imputation is performed in the primary model. To test the robustness of the primary outcomes against potential departures from the MAR assumption (e.g., missing not at random), sensitivity analyses will be conducted using multiple imputation (MI) under MAR and pattern mixture models (PMMs) with delta-adjustment. Sensitivity analyses will also be conducted using the per-protocol set (PPS) to verify that the missing data pattern does not substantially alter the main findings. Additionally, paired *t*-tests will be performed as a supplementary analysis to evaluate overall within-subject pre- and post-treatment changes. Furthermore, potential assessment mode differences (in-person vs. telephone follow-up) will be evaluated by including assessment mode as a covariate or subgroup factor in secondary analytic models.

Safety monitoring data will be descriptively summarized, focusing on the frequency, intensity, and causal relationships of any recorded AEs. Exploratory subgroup analyses will also be performed based on whether participants received concomitant KM interventions. Where applicable, differences in the AE incidence rates between these subgroups will be evaluated using the chi-square test or Fisher’s exact test.

The full analysis set (FAS) will serve as the primary population for effectiveness outcomes, whereas the PPS and safety analysis set (SAS) will be used for per-protocol and safety evaluations, respectively. The specific criteria for these sets of analyses are outlined below.

FAS: This dataset will comprise all enrolled participants who satisfied the eligibility criteria, received HD on at least one occasion, and provided at least one post-baseline effectiveness measurement.PPS: This subset will consist of FAS participants who successfully completed the entire follow-up period without committing any major protocol violations or noncompliance defined a priori.SAS: This population will include all registered individuals who received at least one HD dose and will undergo subsequent safety monitoring.

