## Abstract

**Objective**: Functional dyspepsia (FD) is frequently treated in Korean Medicine (KM) clinics in South Korea. With the recent inclusion of herbal decoctions (HDs) for FD in the national pilot program for health insurance coverage, the generation of real-world evidence has become an important policy priority. In this study, we aim to evaluate the real-world clinical outcomes and safety of individualized HD-centered KM care in patients with FD in a primary care setting. **Methods**: This multicenter, prospective, single-arm observational cohort study will enroll 150 participants who meet the Rome IV criteria for FD across 23 KM clinics nationwide. Participants will receive individualized HDs, prescribed at the discretion of the attending physicians, as the primary treatment for 4 weeks. Concomitant KM treatments (e.g., acupuncture, moxibustion, and cupping) are permitted as clinically needed to preserve the pragmatic nature of routine care. The primary outcome is the change in the total symptom score on the Nepean Dyspepsia Index, Korean version (NDI-K), at week 4. Secondary outcomes include the Numeric Rating Scale for overall severity, overall treatment effect, and safety monitoring. Statistical analyses will be performed using mixed models for repeated measures to account for repeated observations and missing data. **Discussion**: This study will evaluate the pragmatic outcomes of individualized HD-centered KM care in routine clinical practice, thereby supporting the external validity of its findings. The findings are expected to provide foundational real-world data for the national HD pilot program, and these data may serve as a reference for healthcare policies and clinical decision-making. Clinical Trial Registration: Clinical Research Information Service (registration number KCT0010254); registered on 11 February 2025.

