#### 2.5.1. Primary Outcome Measure

The primary outcome is the change in the total symptom score of the Korean version of the Nepean Dyspepsia Index (NDI-K) from baseline to week 4. The NDI-K is a validated tool for quantifying the severity of dyspeptic symptoms and their impact on patient well-being. This study will use a 15-item symptom subscale that captures the frequency and intensity of discomfort; higher cumulative values represent a greater symptom burden [13]. As the original NDI comprises distinct symptom and quality-of-life subscales, this study specifically uses the 15-item Nepean Dyspepsia Symptom Index (NDSI) as the primary outcome measure to precisely evaluate core physical discomforts associated with FD, independent of general quality-of-life domains. In accordance with established clinical trial standards employing the NDSI [14], therapeutic efficacy will be evaluated primarily through continuous score reductions in this symptom subscale.

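### In a single-arm study, the baseline-adjusted MMRM's usual standard error for week-4 mean change omits sampling variation in baseline, so the primary test and interval are somewhat anti-conservative

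*Protocol article*

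**What the plan says.** The abstract describes the design: "This multicenter, prospective, single-arm observational cohort study will enroll 150 participants". The primary outcome (2.5.1) is the change in NDI-K total symptom score from baseline to week 4.

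Section 2.10 fixes the primary model as an MMRM of that change, with categorical visit (weeks 2 and 4), "baseline NDI-K score as a continuous covariate, and a visit-by-baseline interaction as fixed effects". On covariance: "An unstructured variance-covariance matrix (or a heterogeneous first-order autoregressive structure [ARH(1)] if the model does not converge) will be applied". On clinics: "participating sites will be included as a random effect in the mixed models". On the test: "Statistical significance will be set at *p* < 0.05". As a supplement, "paired *t*-tests will be performed as a supplementary analysis to evaluate overall within-subject pre- and post-treatment changes".

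Section 2.9 describes the precision expected from 112 evaluable participants and an SD of change of 10–12 points: "The expected margin of error for the mean primary outcome change is approximately 1.85–2.22 points at the 95% confidence level".

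Section 2.10 does not state the baseline value at which the week-4 mean is evaluated, or whether its variance treats baseline as fixed or random.

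**The concern.** This is the standard specification for a two-arm trial. There the baseline term largely cancels from the between-arm contrast, and adjustment brings a real gain in precision. With one arm nothing cancels. The quantity of interest is a single mean change, and part of the uncertainty in that mean comes from which baselines were sampled.

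The least-squares mean at the observed mean baseline equals the raw mean change when data are complete. Its default standard error, however, uses only the residual variance around the baseline regression, as if the population mean baseline were known to equal the sample mean. The estimate stays the same and the reported error shrinks.

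The p-value and any interval for the primary outcome would then overstate certainty. The paired t-test, which uses the full SD of change, would look less precise than the MMRM with no real gain behind the difference.

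**Working it through.** **Inputs from the document.** Enrolled 150, dropout 25%, about 112 evaluable, SD of change 10–12, 95% level (2.9); 23 clinics; significance level 0.05 (2.10; sidedness not stated, two-sided assumed).

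**Input not in the document.** The correlation ρ between baseline and week-4 NDI-K. Assumed range 0.3 to 0.9, with equal SDs at the two times.

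**1. Reproduce the plan's figures.** 150 × 0.75 = 112.5. 1.96 × 10/√112 = 1.85 and 1.96 × 12/√112 = 2.22. Both match section 2.9, so the planned margin is the one for the unconditional mean change.

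**2. Compare the two variances (complete data).**
- Model-based, at the mean baseline: residual variance/n.
- Population mean change: (residual variance + slope²×Var(baseline))/n = (SD of change)²/n.

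The ratio of standard errors is √(1−R²), where R² is the share of the variance of change explained by baseline. With equal SDs, R² = (1−ρ)/2 and the ratio is √((1+ρ)/2).

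**3. Example: ρ = 0.5, SD of change 10.** The SD at each visit is 10/√(2×0.5) = 10, and the slope of change on baseline is ρ−1 = −0.5. Residual variance = 100×(1−0.25) = 75. Omitted term = 0.25×100 = 25. Model SE = √(75/112) = 0.818; full SE = √(100/112) = 0.945; ratio 0.87. The half-width is 1.60 instead of 1.85.

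**4. Across the assumed range.** Coverage = 2Φ(1.96×ratio)−1; n = 112.

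| ρ | SE ratio | Coverage | Type I error | Model half-width (SD 10–12) |
|---|---|---|---|---|
| 0.3 | 0.81 | 88.6% | 11.4% | 1.49–1.79 |
| 0.5 | 0.87 | 91.0% | 9.0% | 1.60–1.92 |
| 0.7 | 0.92 | 92.9% | 7.1% | 1.71–2.05 |
| 0.9 | 0.97 | 94.4% | 5.6% | 1.81–2.17 |
| slope 0 | 1.00 | 95.0% | 5.0% | 1.85–2.22 |

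Simulation with complete data (n = 112, 20,000 runs per ρ) gave 88.9%, 91.4%, 93.0% and 94.5% for ρ = 0.3, 0.5, 0.7 and 0.9. The paired t-test covered 95.0–95.2%, and the SE with the omitted term restored 95.1–95.2%.

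**5. Closer to the planned model.** REML fit, two visits, unstructured covariance, random intercept for 23 sites (assumed SD 1.5 points), n = 150, 25% missing at week 4 completely at random, SD of change 10 before the site effect.

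| ρ | Runs | Empirical SD | Model SE | Coverage | Coverage, corrected SE |
|---|---|---|---|---|---|
| 0.3 | 1,000 | 0.94 | 0.81 | 91.1% | 95.3% |
| 0.5 | 1,000 | 0.94 | 0.86 | 92.6% | 95.1% |
| 0.7 | 300 | 0.94 | 0.92 | 93.3% | 94.0% |

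Monte Carlo error is about √(0.91×0.09/1,000) = 0.9 points for 1,000 runs and √(0.93×0.07/300) = 1.5 points for 300. The loss is smaller than in step 4 partly because the omitted term is divided by all 150 baselines, while the residual term rests on fewer week-4 values. At ρ = 0.5 the omitted term is 25/150 = 0.167, and √(0.862² + 0.167) = 0.95, in line with the empirical SD.

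**The case against.** The strongest reply is that section 2.10 lists fixed effects and a covariance structure but no interval, evaluation point or variance method. The same fixed effects give a valid interval if the variance treats baseline as random, and an analysis plan that is not shown could say so. That stands as a limit: the shortfall follows from the usual extraction of the mean, not from an explicit statement. But the text names the model and no correction, and ordinary output would not supply one.

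A second reply is that inference conditional on the observed baselines is a recognised target. It is, but it does not fit a margin computed from the SD of change, nor the aim of describing routine care for patients generally.

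Third, the consequence is modest. At ρ = 0.5 the half-width is short by 1.85 − 1.60 = 0.25 to 2.22 − 1.92 = 0.30 points, the study calls itself exploratory and hypothesis-generating, and the prespecified paired t-test would expose the discrepancy. All of this lowers the stakes. It does not repair the primary analysis, and the paired test handles neither clustering nor missing visits.

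Stronger readings are tempting but not supported:
- *Coverage as low as 82–86%.* This needs the SD to fall from 12 at baseline to 9 at week 4, for ρ = 0.3 to 0.7. The document gives no such SDs. The reverse, 9 rising to 12, gives about 92–95% by the same formula.
- *The visit terms estimate change for a patient with an NDI-K of 0.* That assumes an uncentred baseline and that the raw coefficients are reported; the text states neither.
- *Section 2.9 is wrong.* Its margin is correct for the unconditional mean change. It is the model's default standard error that does not match it.

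**Conclusion.** The point holds in direction and mechanism. For the population mean change, the usual standard error from the section 2.10 model is too small whenever change depends on baseline, as regression to the mean would lead one to expect in a fluctuating patient-reported score.

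The size is moderate and rests on an assumed correlation: about 1 to 6 points of coverage lost with complete data (ρ from 0.9 down to 0.3, equal SDs), and about 2 to 4 points in the fit with random sites and 25% week-4 missingness (ρ from 0.7 down to 0.3). The test at 0.05 is affected in the same way. There is no loss if the slope is zero.

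A reader might infer that the mean change itself is biased or that the primary result would be invalid. Neither follows: this mechanism affects only the stated uncertainty. It is nonetheless systematic, anti-conservative and in the primary analysis, so it should be put right before the data are analysed.

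**What to change.** Preferred: make baseline, week 2 and week 4 NDI-K three responses in one model, with categorical visit, unstructured covariance and no baseline covariate, and estimate the week 4 minus baseline contrast. The clinic random effect must vary by visit. A clinic intercept that is constant over visits cancels from the contrast and would drop the between-clinic variation in change that section 2.10 sets out to account for. Baseline still informs missing week-4 values under MAR, because it is in the response vector.

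Alternative: keep the section 2.10 model, state that the week-4 mean is evaluated at the observed mean baseline, and state that its variance treats baseline as random. This can be done by adding slope²×Var(baseline)/n, with n the number of participants whose baselines enter that mean, or by a bootstrap that respects clinics. The added term assumes baselines are not themselves clustered by clinic; a bootstrap that resamples whole clinics avoids that assumption.

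Use the same approach for NRS. Baseline as a covariate or interaction can stay in the exploratory models of who improves.

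Cost: a few lines of text and code, and a slightly wider interval. With about 150/23 ≈ 6.5 participants per clinic, the by-visit clinic variances may be poorly estimated, so a fallback for non-convergence should be named. Recruitment is still running (2.11), so the wording can be changed before analysis.
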